### Outcome Measures

The primary outcome measure is the WAB assessment that is divided into four subitems including spontaneous speech, auditory verbal comprehension, repetition, and naming. The original scores of the four items are 20, 200, 100, and 100, respectively. An aphasia quotient (AQ) is calculated using the following formula: AQ = (spontaneous speech + auditory verbal comprehension/20 + repetition/10 + naming/10) × 2. The AQ indicates the severity of aphasia and can be used as an index for evaluating the improvement and deterioration of aphasia. The highest AQ score is 100, and the normal range is 98.4–99.6. AQ <93.8 is considered as aphasia.

In addition to the WAB scores, there are several secondary measures of treatment outcome including BDAE, Boston Naming Test (BNT), speech acoustic parameters, and RS-fMRI. BDAE is used to measure the severity of impaired language function that can be divided into five grades from severe to mild. The BNT is an assessment tool to measure the confrontational word naming of 30 object pictures. The speech acoustic parameters include fundamental frequency, intensity, speaking rate, maximum phonation time, range of voice features, and speech intelligibility. Speech signals are recorded using a laptop at sampling frequency 44.1 K Hz and Praat software is used to extract acoustic parameters.

RS-fMRI data are acquired using a 3.0 T MAGNETOM Skyra scanner (Siemens, Germany). The participants are instructed to lie still with their eyes closed and think of nothing. Functional images are obtained using echo-planar imaging (EPI) pulse sequence with the following parameters: repetition time (TR) = 2,000 ms; echo time (TE) = 30 ms; 35 slices, field of view (FOV) = 224 mm × 224 mm; slice thickness = 3.5 mm; layer spacing 0.7 mm; flip angle (FA) = 90°; acquisition matrix 64 × 64; voxel size = 3.5 mm × 3.5 mm × 3.5 mm. For registration purposes, a set of high-resolution structural images are acquired through a T1-weighted sequence: 192 sagittal slices; slice thickness = 1 mm; TR = 6.6 ms; TE = 3.1 ms; FA = 12°; FOV = 256 mm × 256 mm. The scanning lasted for 8 min and produced 240 brain volumes.

### Data Analysis

Repeated-measures analysis of variances (RM-ANOVAs) are performed to examine differences in the WAB, BDAE, and BNT scores as well as speech parameters across the conditions, with a within-subject factor of phase (pre- vs. post-treatment) and a between-subject factor of group (real vs. sham cTBS). In the *post hoc* analysis, multiple comparisons are corrected with Bonferroni adjustment. Prior to entering the data into the RM-ANOVAs, Kolmogorov–Smirnov test is used to verify whether they are normally distributed. For non-normally distributed measures, the Wilcoxon Signed Rank Test is used for comparison across the conditions. The intention-to-treat (ITT) analysis is used when there are missing data.

The preprocessing of RS-fMRI data is conducted using DPABI software (v. 6.1) on the MATLAB platform (Mathworks, Natick, MA, United States) (Yan et al., 2016). The main steps are as follows: (1) use MRIConvert software (v. 2.1.0, Lewis Center, Eugene, OR, United States) to convert raw data in DICOM format to NIFI format; (2) remove the first 10 slices and correct the remaining 230 slices for slice timing; (3) correct head motion exceeding 3 mm in any direction or head rotation exceeding 3°; (4) spatially normalize the functional images to a standard Montreal Neurological Institute (MNI) space and resample them to a voxel size of 3 mm × 3 mm × 3 mm; (5) apply a band-pass filter (0.01–0.08) for each voxel to reduce the influence of low frequency fluctuation and high-frequency noise (Lv et al., 2018); and (6) smooth the functional data with a 6-mm full width at half maximum (FWHM) Gaussian kernel.

After the preprocessing, regional homogeneity (ReHo), degree centrality (DC), and seed-to-voxel analyses are conducted to measure the local and global functional connectivity within the language networks. ReHo is calculated based on the Kendall’s coefficient of concordance (KCC), which measures the consistency of the time signal between a voxel and surrounding voxels. Higher ReHo values represent better consistency between the local voxel and the regional brain activities. DC values reflect the network connection intensity between a certain voxel and all of the brain, indicating the importance of this voxel as the network node (Zang et al., 2004). One-way ANOVAs are conducted on the ReHo and DC values to explore differences across the conditions within the predefined gray matter mask. The ANOVA F maps are corrected using Gaussian random field (GRF) correction (single voxel *p* < 0.001, cluster level *p* < 0.05). The ReHo and DC values of the peak voxels in the surviving clusters are extracted and entered into SPSS (v. 22) for further analysis. Seed-to-voxel analyses are conducted with *a priori* regions of interest (ROI). The ROIs consist of language-related regions in cerebellar Crus I; IFG pars opercularis; IFG pars triangularis; primary motor cortex (M1); anterior and posterior STG; angular gyrus; anterior and posterior supramarginal gyrus (SMG), which are selected from the AAL atlas (Tzourio-Mazoyer et al., 2002). These ROI-based functional connectivity maps are statistically compared between pre- and post-treatment and between real cTBS and sham stimulation group. Differences across the conditions are considered significant when *p* < 0.05 at the voxel level, with a false discovery rate (FDR) cluster corrected *p* < 0.05.

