**Methods:**

In this randomized, sham-controlled clinical trial, patients (*n* = 40) with chronic post-stroke aphasia received 10 sessions of real cTBS (*n* = 20) or sham cTBS (*n* = 20) over the right cerebellar Crus I+ a 30-min speech-language therapy. The Western Aphasia Battery (WAB) serves as the primary measure of the treatment outcome. The secondary outcome measures include the Boston Diagnostic Aphasia Examination, Boston Naming Test and speech acoustic parameters. Resting-state fMRI data were also obtained to examine treatment-induced changes in functional connectivity of the cerebro-cerebellar network. These outcome measures are assessed before, immediately after, and 12 weeks after cerebellar cTBS intervention.

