To this end, the purpose of the present study is to investigate the short- and long-term effectiveness of cTBS over the right cerebellum in augmenting language recovery in chronic post-stroke aphasia in a randomized, sham-controlled design. In addition to aphasia test batteries and speech acoustic analyses for evaluation of treatment outcome, the resting-state functional magnetic resonance (RS-fMRI) is also used to explore the neural mechanisms underlying aphasia rehabilitation. The previous studies have shown associations between improved spelling or phonemic fluency and increased resting-state functional connectivity between the cerebellum and language-related cortical regions for patients with chronic post-stroke aphasia or healthy individuals following tDCS over the right cerebellum (Sebastian et al., 2016; Turkeltaub et al., 2016). Accordingly, we hypothesize that, following cTBS over the right cerebellum, patients with chronic post-stroke aphasia will exhibit improved language functions and increased functional connectivity within the cerebro-cerebellar language network. This randomized, sham-controlled study provides significant new insights into the therapeutic efficacy of cTBS over the right cerebellum to augment SLT for post-stroke aphasia and the underlying neuroplastic mechanisms.

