## Methods

### Study Design

This is a prospective, randomized, sham-controlled, single-center study (Registration number: ChiCTR210049828) that will be conducted in the Department of Neurorehabilitation, Wuxi Tongren Rehabilitation Hospital, China. Hospitalized patients with chronic post-stroke aphasia are recruited to participate in the study. They are randomly assigned with a ratio of 1:1 to a real or sham stimulation group. Details about the study design and data collection are shown in Figure 1 and Table 1. On the day of enrollment (T0), after the end of cerebellar cTBS intervention (T1), and 12 weeks post-treatment completion (T2), aphasia test batteries and speech acoustic analyses are performed to evaluate language functions in post-stroke aphasia. Also, RS-fMRI data are collected before and after the end of the intervention. This study has been approved by the Ethics Committee of Wuxi Mental Health Center and Wuxi Tongren Rehabilitation Hospital (WXMHCIRB2021LLky078).

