**FIGURE 1 F1:**
[figure not shown]
Flow chart of study procedure. cTBS, continuous theta burst stimulation.

**TABLE 1 T1:** Overview of data collection and study timings.

Study period visits	Pre-enrollment	T0	T1	T2
Relative start of treatment days	−1 week	Day 0	±3 days after intervention	±3 days after 12 weeks of intervention
Screening (in-/exclusion criteria)	×			
Written informed consent	×			
Medical history	×			
Randomization		×		
NIHSS		×		
WAB		×	×	×
BDAE		×	×	×
BNT		×	×	×
Acoustic evaluation		×	×	×
RS-fMRI		×	×	

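### The two-level phase factor gives the 12-week language assessment (T2) no place of its own, so no test of the long-term between-group effect is stated

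*Protocol article*

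**What the plan says.** All of this is in the Protocol article.

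- **Aim (Introduction).** The purpose is to "investigate the short- and long-term effectiveness of cTBS over the right cerebellum in augmenting language recovery".
- **Schedule (Abstract, Methods).** "These outcome measures are assessed before, immediately after, and 12 weeks after cerebellar cTBS intervention".
- **Schedule (Study Design).** After T0 and T1 comes a third assessment: "and 12 weeks post-treatment completion (T2), aphasia test batteries and speech acoustic analyses are performed".
- **Schedule (Table 1).** WAB, BDAE, BNT and acoustic evaluation are marked at T0, T1 and T2, and the T2 window is ± "3 days after 12 weeks of intervention". RS-fMRI is marked at T0 and T1 only.
- **Analysis (Data Analysis).** Repeated-measures ANOVAs are to "examine differences in the WAB, BDAE, and BNT scores as well as speech parameters across the conditions". The same sentence then spells out the factors of the model, and it lists only two levels for phase: "with a within-subject factor of phase (pre- vs. post-treatment) and a between-subject factor of group (real vs. sham cTBS".
- **Follow-on comparisons (Data Analysis).** "In the *post hoc* analysis, multiple comparisons are corrected with Bonferroni adjustment". For non-normal measures the fallback is the Wilcoxon signed rank test. Neither rule names a time point.

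**The concern.** The aim has two time horizons and the schedule has a visit for each, but the model for the language outcomes has a single post-treatment level. Followed literally, it yields one change from baseline per patient and one group-by-phase test. That test cannot show whether an effect seen at the end of treatment is still there 12 weeks later.

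Two things are at stake. The long-term half of the aim has no stated estimate or test, even on the primary outcome. And once both T1 and T2 results exist, the text does not say whether the post-treatment value is T1, T2 or some average of the two, so that choice could be made after the results are seen.

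**Working it through.** The plan gives no figure for this point. The main check sets its statements side by side. Its sample size enters only in step 4, where it is reproduced before use.

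**1. Visits against factor levels**

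| Outcome | Visits in Table 1 | Count | Phase levels in Data Analysis |
|---|---|---|---|
| WAB, BDAE, BNT, acoustics | T0, T1, T2 | 3 | 2 |
| RS-fMRI | T0, T1 | 2 | separate analysis |

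For the language outcomes, 3 − 2 = 1 visit has no level of its own. Two phases would fit the imaging schedule, but the sentence that defines the factor applies it to the language outcomes.

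**2. Test degrees of freedom**

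With k groups, m phases and N patients, the group-by-phase test has (k − 1)(m − 1) and (N − k)(m − 1) degrees of freedom. Inputs: k = 2; N = 40 (target) or 32 (16 per group, Sample Size section).

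- As written, m = 2: (1, 38) at N = 40; (1, 30) at N = 32.
- With all three visits, m = 3: (2, 76) at N = 40; (2, 60) at N = 32.

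A single interaction degree of freedom carries one contrast. Two horizons need two.

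**3. What can happen to T2 under the stated model**

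- *Left out.* There is no 12-week result.
- *Pooled with T1.* With equal weights, pooled effect = (effect at T1 + effect at T2)/2. Let r be the T2 effect divided by the T1 effect; then pooled/T1 = (1 + r)/2. The article gives no value for r. Assumed values from 0 (effect gone) to 1 (effect fully kept) give 0.5 to 1.0. Whatever r is, the pooled result does not tell the two horizons apart.
- *Handled in a second two-level model, T0 against T2.* This would answer the aim, but the text does not state it or say which model would be primary.

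The other analysis rules do not settle the matter. A two-by-two design also has simple-effect comparisons to which a Bonferroni rule applies, so that rule does not imply a third level. The signed rank test compares two paired conditions.

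**4. Does a named T2 contrast need more patients?**

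The Sample Size section goes from 16 to 20 per group for 20% dropout: 16/(1 − 0.2) = 20, which reproduces. The metric of its effect size of 0.5 is not stated. By the normal approximation, n per group = 2(z for alpha + z for power)²/d². Read as d = 0.5 (two-sided), this gives 63. Read as Cohen's f = 0.5, so d = 1.0 for two groups, it gives 2(1.960 + 0.842)² = 15.7, rounded up to 16. I use d = 1.0 here only because it reproduces the plan's 16; the metric is a separate matter.

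- One primary contrast, T2 secondary: n is unchanged.
- Both contrasts co-primary at 0.025 each (my assumption, not in the article): 2(2.241 + 0.842)² = 19.0, rounded up to 20 evaluable; 20/0.8 = 25 enrolled per group. Power per contrast is about 72% with 16 evaluable per group and 82% with 20.

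**The case against.** The strongest reply is that nothing says T2 is excluded. The Study Design section itself describes T2 by its distance from the end of treatment, so the post-treatment level could be meant to cover it. The analysis section also speaks of ANOVAs in the plural, which leaves room for separate T0–T1 and T0–T2 models. The plural may reflect only the several outcomes, but the reading cannot be ruled out. Besides, a journal article condenses a fuller protocol.

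Much of this stands, and it limits the point. A reader might infer that the 12-week data will go unanalysed and that the long-term aim cannot be answered; the article does not support that. Nor does it support saying that a third of the language assessments (40 of 120) is wasted. That holds only if T2 is dropped and all 40 patients attend, while the plan allows for 20% dropout (40 × 0.8 = 32). Nor is there a basis for one dilution figure, since the course of the effect after T1 is unknown.

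A reader might also fault the plan for not naming group-by-phase as the treatment test, given that both arms receive speech-language therapy. That interaction is already part of the stated ANOVA, and which term is read as the treatment effect is a detail an article may leave out.

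The reply does not remove the mismatch. The article does not merely omit the factor levels. It fixes them at two, against its own three-visit schedule and two-horizon aim.

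**Conclusion.** The point holds in a limited form. The stated analysis of the language outcomes conflicts with the article's own schedule and aim, and no test of the 12-week between-group effect is stated. In size: one of three scheduled visits has no level in the model, and one of two time horizons has no named contrast, for the primary and the secondary language measures alike. If the post-treatment level means T1, the short-term comparison is specified and unaffected.

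The conclusion rests on the text of the article alone. A fuller protocol or analysis plan may say how T2 is handled, but one that used three levels would then differ from this text. The conclusion does not depend on the effect-size metric, on any dropout figure or on any assumed course of the effect.

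**What to change.** In the Data Analysis section, for WAB, BDAE, BNT and speech parameters:

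1. Define phase as a factor with three levels: T0, T1 and T2.
2. Name two group-by-phase contrasts, real minus sham: T1 minus T0 for the short-term effect and T2 minus T0 for the long-term effect.
3. State which of the two is primary for WAB-AQ.

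The contrasts must be named. The overall interaction on 2 degrees of freedom would not by itself say at which visit the groups differ. A linear mixed model using all available visits is an option, with some appeal given the expected dropout, but the correction does not need it.

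**Cost.** The T2 visits are already scheduled, so this is a change of wording plus one more contrast. No extra patients are needed if only one contrast is primary. Making both co-primary would raise the target to 25 per group under the assumptions in step 4 of the working. Testing T2 only after T1 avoids splitting alpha, but a non-significant T1 result then bars a confirmatory claim at T2. That should be weighed against the importance of the long-term aim. The choice should be recorded before the results are seen.

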### Participants

The inclusion and exclusion criteria of the present study correspond to the guidelines for using rTMS in clinics and research (Wassermann, 1998; Rossi et al., 2009; Rossini et al., 2015). Participant inclusion criteria are: (1) patients aged 40–80 years; (2) first-ever unilateral ischemic stroke on the left hemisphere; (3) longer than 6 months post-stroke; (4) non-fluent aphasia as confirmed by the Western Aphasia Battery (WAB); (5) right-handed, native-Chinese speakers without experience of professional vocal or instrumental training; (6) Boston Diagnostic Aphasia Examination (BDAE) Grades I–III; and (7) elementary education level and above, with normal or corrected to normal vision. Participant exclusion criteria are: (1) history of substance or alcohol abuse, premorbid seizures, or neuropsychiatric diseases; (2) contraindications involving TMS and fMRI (e.g., skull defect or skin damage at the stimulation site, intracranial implant, cardiac pacemaker, and implanted drug pumps); (3) history of neurosurgical treatment; (4) unable to cooperate with assessment and treatment due to severe cognitive impairment; and (5) other neurological disease. All participants provide written informed consent prior to participating in the study.

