### Sample Size

The sample size was calculated using PASS software (v.15.0) on the basis of previous studies. With an effect size of 0.5 based on the WAB-AQ (Hu et al., 2018), we expect that the target effect size had 80% of power with a type I error of 5% (α = 0.05). Thus, the sample size of each group is at least 16. With an assumption of 20% dropout rate, a sample size of 20 participants will be targeted for each group.

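### The normality test is applied to the scores, not to within-patient change, so it can move an outcome, including the primary WAB, from a valid between-arm test to a paired test that does not compare arms.

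*Protocol article*

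**What the plan says.** The Data Analysis section plans repeated-measures ANOVAs to "examine differences in the WAB, BDAE, and BNT scores as well as speech parameters across the conditions". The model is specified "with a within-subject factor of phase (pre- vs. post-treatment) and a between-subject factor of group (real vs. sham cTBS". A gate comes first: "Prior to entering the data into the RM-ANOVAs, Kolmogorov–Smirnov test is used to verify whether they are normally distributed". Outcomes that fail it leave the model: "For non-normally distributed measures, the Wilcoxon Signed Rank Test is used for comparison across the conditions".

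What is tested is the data entered into the model, that is, the scores. Change and residuals are not mentioned. The section does not say whether arms and visits are tested separately or pooled, or whether the K-S test is corrected for estimating the mean and SD (Lilliefors form).

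The rule covers the primary outcome, WAB. It also covers BDAE, of which Outcome Measures says: "BDAE is used to measure the severity of impaired language function that can be divided into five grades from severe to mild". Under Participants, entry is limited to "Boston Diagnostic Aphasia Examination (BDAE) Grades I–III".

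**The concern.** The term of this two-factor model that compares the treatment effect between arms is the group-by-phase interaction. With two phases it depends only on each patient's change, because the patient's own level cancels. The gate looks at the level. Patients admitted across a range of severity can give spread, skewed or clustered WAB scores while their changes are well behaved.

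An outcome that fails the gate does not get another between-arm test. The signed rank test is paired: it asks whether scores moved within a set of patients. All participants receive speech-language therapy, so a gain common to both arms is plausible, and a paired test would read it as an effect. The randomised comparison of the primary outcome could thus be dropped because patients differ in severity at entry.

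**Working it through.** **Planned size.** Sample Size gives 16 per group, raised to 20 for 20% dropout. Reading the stated 0.5 as Cohen's f (d = 1.0), with two-sided 0.05 and 80% power: n = 2(1.96 + 0.842)²/1² = 15.7, so 16; and 16/(1 − 0.20) = 20. (Read as Cohen's d it would need 63 per group; that is a separate matter.) The checks below use 20 per arm and a 1-SD arm effect in change.

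**Step 1: what the F-test rests on.** Let d be post minus pre. For two phases and two arms, F(group × phase) = (mean d in real − mean d in sham)² / [s²(1/n₁ + 1/n₂)], where s² is the pooled variance of d. This is the squared two-sample t on change. On a test data set both came to 0.002749.

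**Step 2: how often the gate misdirects.** Assumed: normal change with SD 6, and switching when any of the four arm-by-visit cells fails at 5%. At n = 20 the critical value is about 0.192 for Lilliefors and 0.294 for uncorrected K-S. The protocol gives no WAB distribution, so the baseline shapes are assumptions. Ranges cover the variants tried.

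| Baseline shape | Lilliefors flags | Uncorrected K-S flags |
|---|---|---|
| Normal | 17% | near 0% |
| Uniform | 26–28% | near 0% |
| Skewed | 74–90% | 4–7% |
| Clustered | 83–100% | 4–35% |

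The 17% is the false-alarm rate of four tests: 1 − 0.95⁴ = 18.5% if independent, and slightly less because pre and post are correlated. A Lilliefors check on change in each arm flags about 10% (1 − 0.95² = 9.75%), whatever the baseline shape.

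**Step 3: was the between-arm test valid?** Yes. With normal change the interaction test rejected in about 5% of trials under no arm effect, for every baseline shape. Power for a 1-SD arm effect was about 87% (noncentrality 1 × √(20/2) = 3.16).

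**Step 4: what the fallback does.** With a common 4-point gain and no arm effect, the signed rank test of pre against post in the real arm rejects in about 76–80% of trials. The approximate noncentrality is (4/6) × √20 = 2.98.

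**Step 5: the opposite error.** With a normal baseline and exponential or lognormal change, Lilliefors on the scores flags about 17%, which is only its false-alarm rate. On change it flags 82–96%. The F-test still holds its size: about 4.8% with exponential change and 3.9% with lognormal change. The cost is power: for lognormal change with a 2.5-fold arm effect, 61% against 79% for a between-arm rank test on change.

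**Step 6: uncorrected K-S.** At n = 20 its true level is about 0.0001 or lower. It misses exponential data 96% of the time and lognormal data (sigma 0.8) about 90%.

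**Step 7: BDAE.** Three baseline grades fail Lilliefors in 100% of samples. Uncorrected K-S fails them in about 21% for equal grade shares, and in up to 90% for the uneven shares tried.

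**The case against.** The strongest reply is that the damage comes from the fallback, not the gate. If failing outcomes went to a rank-sum test on change, misdirection would cost almost nothing: power of 84–86% against 86–87% for the t-test under normal change. This stands in part. The loss of the between-arm comparison needs both the gate and the paired test. But the article names the paired test, and replacing it alone would leave the choice of primary analysis to a check on the wrong quantity.

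A second reply is that the scores are not irrelevant. Jointly normal pre and post scores imply normal change, and raw-score shape does matter for the group main effect. This also stands. A reader might infer that the gate is unrelated to the assumption, but it is an imperfect proxy. Separate tests at each visit cannot establish joint normality, however, and the group main effect does not estimate the effect on change.

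A third reply is that the high flag rates need the Lilliefors form, a skewed or clustered baseline and an any-cell trigger, none of which the article states. That is correct. A reader might infer that WAB will probably lose its between-arm test; the documents do not support this. With uncorrected K-S and most of the shapes tried, it would usually stay. Nor does the text support a choice that differs by visit, since it switches by measure.

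Finally, an article may leave the details of a normality check to a fuller plan. The form of K-S is such a detail, but the object of the test and what follows failure are stated here.

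**Conclusion.** The point holds as a flaw in a stated decision rule. Scores are tested where within-patient change or residuals matter, and failure moves an outcome, possibly the primary one, to a test that does not compare arms. That is the material harm.

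Its frequency cannot be fixed from the document. Under the stated assumptions it runs from near 0% to nearly all trials, depending on the WAB distribution and the K-S form. Either form is unsatisfactory: Lilliefors can eject a valid analysis because severity varies, and uncorrected K-S passes almost anything continuous unless it is strongly clustered.

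A reader might also infer that skewed change which slips through makes the F-test invalid. It does not: type I error stayed at or below about 5% with equal arms of 20, so the cost is power. For BDAE, near-certain failure applies to Lilliefors only, and moving an ordinal grade to a rank method is reasonable in itself; the fault there is the paired test. If the 12-week visit were added as a third phase, the interaction would rest on several within-patient contrasts and the point would remain.

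**What to change.** Delete the K-S gate and its switch. Before unblinding:

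- **WAB-AQ:** name one between-arm primary analysis, either the group-by-phase test (the comparison of change) or its baseline-adjusted form, but not both. Do the same for BNT and the acoustic measures.
- **Checking:** inspect model residuals rather than raw scores, and do not let the inspection change the primary analysis.
- **Sensitivity:** pre-name a between-arm rank-sum or permutation test on change.
- **BDAE:** name a between-arm rank or ordinal analysis outright.

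The cost is two reworded sentences and one extra sensitivity analysis per outcome. No patients or data are added, and the sample size is unaffected. The sponsor gives up the option to switch tests after seeing the data.

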### Interventions

The application of cerebellar cTBS is administered using Magneuro 100 (Vishee Medical Technology Co., Ltd., Nanjing, China) equipped with a figure 8-shaped coil (7 cm out diameter). Before intervention, a single-pulse TMS will be applied over the right primary motor cortex to determine active motor threshold (AMT). The AMT is defined as the lowest stimulus intensity that produces a motor evoked potential (MEP) of >200 μV in at least 5–10 consecutive trials with 10% maximal voluntary contraction of the first dorsal interosseous muscle of the non-paretic hand (Koch et al., 2020). Each participant receives real or sham cTBS over the Crus I of the right lateral cerebellum (3 cm right and 1 cm inferior to the inion) at 80% of AMT (Lin et al., 2022). A standard cTBS protocol consists of bursts of 3 pulses at 50 Hz that are repeatedly presented at 5 Hz, resulting in a total of 600 pulses in 40 s. The coil is oriented vertically to the target with the handle pointing superiorly during real stimulation; while the stimulation face of the coil is turned 90°, so that the side of the coil is placed on the target during sham stimulation (Rastogi et al., 2017). Immediately following real or sham cerebellar cTBS, all participants receive a 30-min SLT that includes training on comprehension, expression of spoken language, semantic, and phonological processing. The content of SLT will be modified based evaluation of language function on an individual level. Totally, each participant receives 10 sessions of cerebellar cTBS coupled with SLT (5 sessions per week) within 2 weeks.

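### For measures that fail the normality check, the only fallback named is a paired test, so no valid real-versus-sham comparison is stated for them

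*Protocol article*

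**What the plan says.** The Data Analysis section uses repeated-measures ANOVA to examine "differences in the WAB, BDAE, and BNT scores as well as speech parameters across the conditions". The conditions are defined by two factors: "with a within-subject factor of phase (pre- vs. post-treatment) and a between-subject factor of group (real vs. sham cTBS"). Before the ANOVA, a "Kolmogorov–Smirnov test is used to verify whether they are normally distributed". The fallback follows: "For non-normally distributed measures, the Wilcoxon Signed Rank Test is used for comparison across the conditions".

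The section names no other non-parametric method for these outcomes: no rank-sum test, rank-based ANCOVA, ordinal model or transformation.

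Three other statements bear on the point:

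- Study Design, on the arms: "They are randomly assigned with a ratio of 1:1 to a real or sham stimulation group". No matching of patients across arms is described.
- Outcome Measures, on one of the tested measures: "BDAE is used to measure the severity of impaired language function that can be divided into five grades from severe to mild". The Participants section limits entry to grades I–III.
- Interventions, on the background treatment: "Immediately following real or sham cerebellar cTBS, all participants receive a 30-min SLT".

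**The concern.** The trial asks whether real cerebellar cTBS adds to SLT beyond sham. In the ANOVA, the group-by-phase interaction answers that. The fallback replaces the whole analysis for a non-normal measure, and the conditions it is meant to compare include group. A signed-rank test needs two values from the same unit, and patients in different arms supply no such pair.

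What remains is a pre–post test in each arm. Because both arms receive SLT, both may improve, so a significant change within the real arm does not isolate a cTBS effect. An analyst following the text would have to pair patients arbitrarily, choose another test after seeing the data, or set two within-arm p-values side by side. The rule covers the primary WAB outcome as well as BDAE, BNT and the speech parameters.

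**Working it through.** The article states no figure here to reproduce. The check has three parts.

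**1. Test against design**

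| Comparison | Data structure | Can signed-rank test it? |
|---|---|---|
| Pre vs post within an arm | Paired | Yes |
| Real vs sham | Two independent samples, 1:1 randomised | No |
| Group by phase (difference in change) | Two independent samples of changes | No |

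Forcing the arms into arbitrary pairs does not rescue it. In one simulated data set of 20 against 20, re-ordering the patients alone moved the signed-rank p-value from 0.0003 to 0.20. With unequal arms (20 against 19) the test cannot be run, and the 20% dropout assumed under Sample Size makes unequal arms likely.

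**2. How often the fallback would be triggered**

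From the article: planned sizes of 16 per arm after dropout and 20 per arm enrolled (40 pooled); BDAE in five grades, with I–III at entry. Assumed: three equally likely grades, tested at 5%.

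| Version of the check | Rejects normality |
|---|---|
| Lilliefors-corrected, per arm (n = 16 to 20) | 95% to 100% |
| Uncorrected, mean and SD estimated, both arms pooled (n = 40) | about 86% |
| Uncorrected, mean and SD estimated, per arm (n = 16 to 20) | about 9% to 21% |

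Unequal three-grade splits raise the uncorrected per-arm rate, to 77% at the highest tried. After treatment all five grades are possible. With an assumed 10/20/40/20/10% split, Lilliefors rejects in 69% (n = 16) and 82% (n = 20), and the uncorrected test in 6% and 8% per arm and 52% pooled.

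For an AQ-like score, assumed to follow 100 × Beta(2,3), Lilliefors rejects in 6% (n = 16), 6% (n = 20) and 9% (n = 40). For a score uniform on 20–80 it rejects in 8%, 9% and 21%.

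**3. Error rate if benefit were read from the within-arm tests**

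Assumed: no cTBS effect, the same true gain in both arms in units of the SD of change, skewed (gamma, shape 2) changes, two-sided 5%, 3,000 simulated trials per cell. The inference rule (real significant, sham not) is also an assumption.

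| True gain in both arms | Real only, n = 16 | Real only, n = 20 | Rank-sum on change, n = 16 / 20 |
|---|---|---|---|
| 0 | 7.4% | 7.8% | 4.4% / 5.4% |
| 0.3 SD | 8.6% | 11.3% | 4.5% / 5.1% |
| 0.5 SD | 23.3% | 26.8% | 5.1% / 5.1% |
| 0.7 SD | 18.7% | 12.5% | 4.3% / 4.5% |
| 1.0 SD | 0.3% | 0.03% | 4.8% / 4.4% |

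Normal changes give the same pattern: about 4% at no gain, 15–19% at 0.3 SD, 24–26% at 0.5 SD, 14–21% at 0.7 SD and 2–5% at 1 SD.

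A formula confirms the shape. If each arm's test is significant with probability π, independently, then P(real only) = π(1 − π). At n = 16 and 0.5 SD, π = 0.359, giving 0.359 × 0.641 = 0.230, against 0.233 simulated. The maximum is 0.5 × 0.5 = 25%, so simulated values of 26–27% are simulation error around that ceiling.

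**The case against.** Several points on the other side are fair.

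- **Normal measures are untouched.** A measure that passes the check keeps the ANOVA, whose interaction validly compares real with sham. This stands. A reader might infer that the primary outcome has no valid test. The article does not support that: AQ loses its comparison only if it fails the check, and under the two assumed AQ distributions it usually passes. Its true distribution is unknown.
- **Triggering is not certain.** A reader might infer that BDAE is bound to fail. That holds nearly always with the Lilliefors correction and usually on pooled data, but not with the uncorrected test in each arm, and the article does not specify the version.
- **No decision rule is stated.** A reader might infer that success will be declared when the real arm is significant and the sham arm is not. The article never says so. The error rates in part 3 belong to that assumed rule, and 0.5 SD lies near the peak of the curve.
- **The signed-rank test has a proper use**, as a within-arm description. Agreed, but the text makes it the replacement for a comparison that includes group.
- **An analysis plan may settle it, or the name may be a slip for rank-sum.** Either is possible. But the article names an unsuitable test rather than deferring the choice, so the sentence needs correcting in either case.

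**Conclusion.** The point holds, limited to measures that fail the normality check: for those, the stated fallback cannot compare the randomised arms, and no valid real-versus-sham test is given. This follows from the test's definition and the parallel-arm design, and needs no assumption.

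The practical size does depend on assumptions. BDAE is the most exposed, with a trigger rate anywhere from about 9% to 100% for an equal three-level grade, according to the version of the check and the sample it is applied to. Exposure of the primary AQ is possible but not shown to be likely. If within-arm results were used to claim benefit, the false-positive rate over gains of 0 to 1 SD would lie between about 1% or less and about 25% (27% as simulated). It would depend on an SLT gain that the article does not give, so it is not controlled at 5%.

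**What to change.** In Data Analysis, replace the signed-rank fallback with a between-arm test: the Wilcoxon rank-sum (Mann–Whitney) test on change from baseline at T1 and at T2. State that the signed-rank test serves only to describe change within each arm.

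Rank ANCOVA with the baseline value, or an ordinal model for BDAE adjusted for baseline grade, are optional alternatives. The ordinal model may be unstable with 16–20 patients per arm and sparse grades. Fixing the method for each outcome in advance, instead of by a normality pre-test, is likewise a preference and not needed to cure the error.

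The cost is about one sentence, with no extra data, visits or patients.
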